### Provisions post-trial care

If a participant suffers harm as a result of their involvement in the study, the Sponsor has a specialist insurance policy in place that would operate in the event of any participant suffering harm as a result of their involvement in the research (Newline Underwriting Management Ltd, at Lloyd’s of London).

### Participant timelime

Enrolment is the day that the informed consent form is signed, and the participant is enrolled in the study. Enrolment may be any day once the diagnostic sample is taken or after the patient has been considered a “presumptive case” by their treating clinician.

After enrolment, days are counted from the date the diagnostic sample is taken:

Day 1 is the date that the first sample to diagnose mpox was taken, regardless of when results became available. If the participant is enrolled on the same day that the diagnostic sample is taken, enrolment occurs on Day 1.If a participant is enrolled after the date that the diagnostic sample was taken, then study procedures start from the number of days since the sample was taken.

Participants who do not receive treatment follow the schedule from D1 and continue until D180. Participants who receive treatment immediately following diagnosis and enrolment in the study follow the schedule described above.

If a participant enters the study without receiving treatment and then begins receiving treatment at a later date, they initiate a new schedule of procedures by restarting at D1. This second D1 represents the date of treatment start. This extends the study participation period by the number of days between enrolment and treatment initiation.

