**Methods:**

MOSAIC recruits participants of any age with laboratory-confirmed mpox disease who provide informed consent. Participants enrol in the cohort for a total of six months. Blood, lesion and throat samples are collected at several timepoints from the day of diagnosis or the first day of treatment (Day 1) until Day 28 for PCR detection of hMPXV. Clinical data are collected by clinicians and participants (via a self-completion questionnaire) for six months to characterize the signs and symptoms associated with the illness, as well as short- and more long-term outcomes.

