**Figure 1. f1:**
[figure not shown]
Tiered approach.

**Table 1. T1:** Schedule of procedures.

TIER				Baseline ^ a ^	Study days or Treatment days (D)																	
					D1	D2	D3	D4	D5	D6	D7	D8	D9	D10	D11	D12	D13	D14	D21	D28	D60	D180
**1**	**2**	**3**	*Windows permitted*															*±2 days*		*±2 days*	*±7 days*	*±7 days*
x	x	x	**Baseline assessment**																			
x	x	x	Consent	**X**																		
x	x	x	Demographics	**X**																		
x	x	x	Medical history ^ b ^	**X**																		
x	x	x	**Medical assessment**	**X**	**X**	*For patients who are hospitalised ^ c ^ or if a patient attends a pre-* *scheduled clinic visit*												**X**		**X**	X	X
x	x	x				X	X	X	X	X	X	X	X	X	X	X	X					
x	x	x	**Outcome assessment**															**X**		**X**	X	
x	x	x	**Sampling** ^ d ^																			
x	x	x	Two lesion swabs	**X**				X				X						**X**	X ^ e ^	**X**		
x	x	x	Throat swab	**X**				X				X						**X**	X ^ e ^	**X**		
	x	x	Mucosal lesion swab ^f,g^	X																		
	x	x	Saliva sample (using swab) ^f^	X								X						X		X	X ^h^	X ^i^
	x	x	Anus swab ^f^	X								X						X		X	X ^h^	X ^i^
x	x	x	Blood sample collection ^ e ^	**X**				X				X						**X**	X ^ e ^	**X**		
	x	x	Supplementary blood sample for serum	X				X				X						X		X	X	X
		x	Supplementary blood sample for plasma																	X	X	X
	x	x	Urine sample	X								X						X		X	X ^h^	X ^i^
	x	x	Semen or vagina secretions sample	X								X						X		X	X ^h^	X ^i^
x	x	x	**Participant self-assessment survey**	X	X	X	X	X	X	X	X	X	X	X	X	X	X	X	X	X	X	X
	x	x	**Participant social and sexual** **behaviour self-questionnaire**	X																		

*Note:* X in bold are data collection and sampling timepoint to prioritise.

^a^Baseline (could be anytime from D1) – baseline assessment and baseline medical assessment are done at enrolment; baseline samples are the participant’s diagnostic samples, which may have been collected for routine care before study participation commenced.

^b^Includes comorbidities, results of pregnancy and human immunodeficiency virus (HIV) tests, data on signs and symptoms experienced by the participant since their mpox diagnostic sample was collected, and details of potential adverse events (AEs) and serious adverse events (SAEs) occurring since their mpox diagnostic sample was collected.

^c^For hospitalised participants, hospital assessments should continue daily until the point of discharge

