### Data collection methods

All data are recorded by the clinical and study teams directly on the REDCap (version 13.1.30)
^
9
^ electronic Case Report Form (eCRF) for each timepoint as defined in
Table 1.

**
*Demographics and medical history.*
** Data relating to the participant’s demographics and medical history are collected at baseline. Demographic includes sex at birth and ethnic group. Medical history includes data on comorbidities, results of pregnancy and HIV tests, data on signs and symptoms experienced by the participant between the collection of mpox diagnostic sample and the point of consent, and details of potential AEs and SAEs occurring between the collection of mpox diagnostic sample and the point of consent.

**
*Medical assessments.*
** Medical assessments are undertaken at baseline, and D14, 28, 60, and 180. These assessments can be conducted in person,
*via* video link or telephone. The data collected include the participant’s signs and symptoms, any treatment they may be receiving for mpox, AEs and SAEs details.

**
*Biologic sampling.*
** Baseline samples are the participant’s diagnostic samples that may have been collected under routine care before the participant signed the consent form. Blood* (~0.5ml to 20ml depending on local collection procedures), two lesion swabs and one throat swab are collected at D4*, 8*, 14, 21* and 28 where feasible to do so and permitted under local and national regulations–the asterisk (*) denotes procedures only for hospitalised subject; day 21 and 28 sampling only if day 14 sample is still positive.

Where local capacity limits sample collection, sites should prioritise the collection of D14 and 28 samples. All samples are tested by PCR only conducted in local laboratories in each participating country.

In Tier 2 in France, in addition to the sampling covered in Tier 1, additional samples of mucosa, saliva, anus, urine, semen or vaginal secretions, and blood are collected at baseline, D8, D14, D28, D60 (in case of oral, genital or anal lesion) and D180 (only if sample is positive at D60).

In Tier 3 in France, in addition to the sampling covered in Tier 1 and 2, additional samples of blood are collected at D28, D60 and D180.

Samples in Tier 2 and 3 are tested as in
Table 2.

**Table 2. T2:** Tests by sample type.

TIER	Test	Sample							
		Lesion	Throat	Mucosal lesion	Saliva	Anus	Blood	Urine	Semen or vagina secretion
1	PCR	X	X				X		
1&2	Bacterial STIs detection		X			X	X	X	

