Regarding virologic endpoints, the analysis will present the medians and interquartile ranges of mpox virus levels, measured in Cycle threshold (Ct) values, at different time points including baseline, and on days 4, 8, 14, and 28. These measurements will be used to assess viral clearance, categorized as a binary variable, in blood, skin lesions, and throat. The frequency of viral clearance will be reported based on the day of follow-up and treatment status groups.

Additionally, change in mpox virus DNA levels in throat and blood swabs will be compared to baseline on days 4, 8, 14, and 28 and will compared between treatment status using linear regressions at each timepoint.

Logistic regressions will model the presence of mpox virus DNA in lesion swabs at each timepoint.

Regarding safety endpoints, the number and type of SAEs, SARS and SUSARs within 28 days of enrolment will be described.

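### When treatment starts after entry, Day 1 restarts but the virologic baseline does not, so treated and untreated changes from baseline at the same nominal day span unequal intervals

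*Protocol article*

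**What the plan says.** All references are to the Protocol article.

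- **Clock.** The Participant timeline section sets the general rule: "Day 1 is the date that the first sample to diagnose mpox was taken, regardless of when results became available". For someone who enters untreated and is treated later, "they initiate a new schedule of procedures by restarting at D1", and "This second D1 represents the date of treatment start". Those treated immediately after diagnosis and enrolment keep the first schedule.
- **Baseline.** Table 1, footnote a: "baseline samples are the participant’s diagnostic samples, which may have been collected for routine care before study participation commenced". Footnote d repeats this, and the Data collection methods section agrees: "Baseline samples are the participant’s diagnostic samples that may have been collected under routine care before the participant signed the consent form". None of the three makes an exception for a restarted schedule.
- **Sampling days.** For Tier 1 lesion swabs, throat swab and blood, Table 1 marks Baseline, D4, D8, D14, a conditional D21 and D28. The D1 column is empty for all three. The abstract is looser, describing sampling "from the day of diagnosis or the first day of treatment (Day 1) until Day 28".
- **Analysis.** The Outcomes section defines change from baseline in throat and blood at D4, D8, D14 and D28. The statistical section says that this change "will be compared to baseline on days 4, 8, 14, and 28 and will compared between treatment status using linear regressions at each timepoint".

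**The concern.** A change score compares groups fairly only if both groups' changes run over comparable time. Here late starters are measured from a sample taken L days before their second D1, while the visit label counts only from that D1. Whatever viral load does in those L untreated days enters the treated change and is absent from the untreated one. In a self-limiting infection the expected course after diagnosis is a fall in load (a rise in Ct), so part of the natural decline could be read as a drug effect.

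At stake are the secondary virologic comparisons in throat and blood, which bear on whether an antiviral appears active. The treated group is small, so a modest number of late starters can move its mean.

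**Working it through.** The plan states no sample size, power or expected virologic difference, so there is no figure of its own to reproduce.

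**Step 1: elapsed days (from the document's rules alone).** Put the diagnostic sample at time 0.

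- Untreated: nominal day d falls at d - 1 days.
- Treated L days later: the second D1 falls at L, so nominal day d falls at d - 1 + L days.

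| Nominal day | Untreated | L = 2 | L = 4 | L = 7 | Ratio at L = 4 |
|---|---|---|---|---|---|
| D4 | 3 | 5 | 7 | 10 | 7/3 = 2.33 |
| D8 | 7 | 9 | 11 | 14 | 11/7 = 1.57 |
| D14 | 13 | 15 | 17 | 20 | 17/13 = 1.31 |
| D28 | 27 | 29 | 31 | 34 | 31/27 = 1.15 |

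The values of L are illustrative; the document gives none.

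**Step 2: bias with no drug effect.** With f the share of treated participants who start late, s the natural Ct rise per day and L the lag, the spurious difference in mean change is f × s × L. All three inputs are assumptions.

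- Smallest case: 0.25 × 0.25 × 2 = 0.125, about 0.1 Ct.
- Largest case: 1 × 1.0 × 7 = 7 Ct.
- Middle cases, f = 0.5 and L = 4: s = 0.25, 0.5 and 1.0 give 0.5, 1.0 and 2.0 Ct.
- Load still rising, s = -0.5, f = 0.5, L = 4: -1.0 Ct, against treatment.

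**Step 3: effect on a nominal 5% test.** The Discussion reports 601 cases: 55 treated with tecovirimat, 7 with cidofovir and 2 with both. Counting the 2 separately, 55 + 7 + 2 = 64 are treated and 601 - 64 = 537 untreated. Assume an SD of change of 5 Ct. Then SE = 5 × √(1/64 + 1/537) = 0.66 if everyone is sampled, and 0.66 × √2 = 0.94 if half are. The normal-approximation rejection rate is Φ(b/SE - 1.96) + Φ(-b/SE - 1.96).

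| Bias b (Ct) | All sampled | Half sampled |
|---|---|---|
| 0.5 | 12% | 8% |
| 1.0 | 33% | 19% |
| 2.0 | 86% | 57% |

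These rates only illustrate sensitivity. Actual numbers at each day will be lower, especially at D4 and D8.

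**Step 4: change over follow-up.** The product f × s × L ignores the PCR ceiling. An illustrative simulation used a baseline Ct of mean 25 (SD 5), a rise of 0.8 per day (SD 0.3), measurement noise of SD 2, a ceiling at Ct 40, and every treated participant starting 4 days late. The spurious difference was about 3.1 Ct at D4, 2.8 at D8, 1.9 at D14 and 0.4 at D28.

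**Step 5: after correction.** If both groups' change is taken over the same elapsed time since diagnosis, the L extra days drop out, this bias is 0 and the rejection rate returns to 5%.

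**The case against.** The strongest reply is that an analysis plan, not shown, will settle how a late starter's change score is derived. The protocol leaves data transformations and confounder adjustment to it, and never says in one sentence that a restarted participant's change uses the older sample. That conclusion comes from joining three sections. This carries some weight, but the protocol does fix the baseline, three times and without exception, and the example confounders it names (age, vaccination, extent of lesions) would not correct an unequal interval.

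Several stronger readings are tempting but not supported.

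- A reader might infer that late starters have no pre-treatment sample after diagnosis. The document does not establish this. The abstract can be read as including a sample on the first treatment day, and a D4 or D8 sample from the first schedule may precede a later first dose. The rules simply do not make any such sample the baseline.
- A reader might infer that the bias must favour treatment. That depends on load falling after diagnosis; Step 2 shows the reversal.
- A reader might infer that all throat and blood comparisons at all four days suffer alike. The Data collection methods section limits D4 and D8 sampling, and blood, to hospitalised participants, and D28 to those still positive at D14. The ceiling also shrinks the bias late in follow-up.
- A reader might infer that the problem would survive agreement on a single visit clock. If every participant's days were counted from the diagnostic sample, it would vanish. It arises from a second time origin combined with an unchanged baseline.

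The restart clause also covers only those who enter untreated and are treated later. Nothing in the document says how many they are.

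**Conclusion.** The point holds as a structural mismatch. For late starters, the stated rules give a throat and blood change from baseline that spans L days more than the untreated change with which it is compared at the same nominal day. That follows from the text without assumptions.

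Direction and size do not. The bias favours treatment if load falls naturally after diagnosis and reverses if load is still rising before treatment. Lag, share of late starters, slope and SD are not given. Over assumed shares of 0.25 to 1, lags of 2 to 7 days and rises of 0.25 to 1 Ct per day, it runs from about 0.1 to 7 Ct. It is likely largest at D4 and D8, where few are sampled, and small by D28. This concerns secondary endpoints and should be corrected before analysis.

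**What to change.** For the virologic comparison, model Ct on actual days since the diagnostic sample, with treatment as a time-updated covariate. This puts everyone on one time axis and assigns the days before the first dose to the untreated state.

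At minimum, compare change over equal elapsed time by adjusting for the days between the baseline and visit samples. This is the weaker option. At a single nominal day, untreated participants vary little in elapsed time, so the adjustment leans on variation in lag among the treated.

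If a pre-dose sample is used as baseline for late starters, also align or adjust for time since diagnosis. Otherwise treated participants later in their illness are compared with untreated participants at diagnosis.

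Reconcile the abstract, Table 1 with its footnotes, and the Participant timeline section on whether a sample is due on the first treatment day, and state which sample is the baseline after a restart.

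The cost is small: wording, slightly more analysis work, and sample and treatment dates that the schedule already requires. Some late starters lose a simple change score.

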### Data collection methods

All data are recorded by the clinical and study teams directly on the REDCap (version 13.1.30)
^
9
^ electronic Case Report Form (eCRF) for each timepoint as defined in
Table 1.

**
*Demographics and medical history.*
** Data relating to the participant’s demographics and medical history are collected at baseline. Demographic includes sex at birth and ethnic group. Medical history includes data on comorbidities, results of pregnancy and HIV tests, data on signs and symptoms experienced by the participant between the collection of mpox diagnostic sample and the point of consent, and details of potential AEs and SAEs occurring between the collection of mpox diagnostic sample and the point of consent.

**
*Medical assessments.*
** Medical assessments are undertaken at baseline, and D14, 28, 60, and 180. These assessments can be conducted in person,
*via* video link or telephone. The data collected include the participant’s signs and symptoms, any treatment they may be receiving for mpox, AEs and SAEs details.

**
*Biologic sampling.*
** Baseline samples are the participant’s diagnostic samples that may have been collected under routine care before the participant signed the consent form. Blood* (~0.5ml to 20ml depending on local collection procedures), two lesion swabs and one throat swab are collected at D4*, 8*, 14, 21* and 28 where feasible to do so and permitted under local and national regulations–the asterisk (*) denotes procedures only for hospitalised subject; day 21 and 28 sampling only if day 14 sample is still positive.

Where local capacity limits sample collection, sites should prioritise the collection of D14 and 28 samples. All samples are tested by PCR only conducted in local laboratories in each participating country.

In Tier 2 in France, in addition to the sampling covered in Tier 1, additional samples of mucosa, saliva, anus, urine, semen or vaginal secretions, and blood are collected at baseline, D8, D14, D28, D60 (in case of oral, genital or anal lesion) and D180 (only if sample is positive at D60).

In Tier 3 in France, in addition to the sampling covered in Tier 1 and 2, additional samples of blood are collected at D28, D60 and D180.

Samples in Tier 2 and 3 are tested as in
Table 2.

**Table 2. T2:** Tests by sample type.

TIER	Test	Sample							
		Lesion	Throat	Mucosal lesion	Saliva	Anus	Blood	Urine	Semen or vagina secretion
1	PCR	X	X				X		
1&2	Bacterial STIs detection		X			X	X	X	
1&2	HIV-RNA quantification						X		X
1&2	MPXV quantification (sPCR) + infectivity assessment (cell culture)	X	X	X	X	X	X	X	X
1&2	MPXV sequencing	X	X	X	X	X	X	X	X
1&2	Humoral immune response characterisation (anti- MPXV antibodies quantification, seroneutralization)						X		
1&2 &3	Cellular immune response characterisation						X		
1&2	Genetic host factors determination + auto-immune antibodies detection						X		
1&2	Tecovirimat pharmacokinetics						X		

HIV, human immunodeficiency virus; MPXV, mpox virus.

Please refer to ‘Additional File 2: Appendix F’ in
*Extended data* for further information on sample processing, analysis and storage in the UK
^
7
^.

**
*Participant self-assessment survey.*
** All participants are asked to complete a self-assessment survey from the point of entry into the study until D180
*via* a secure online questionnaire. The questionnaire, completed
*via* online REDCap survey, captures information about the participant’s signs and symptoms, including lesion status.

For Tier 2 and Tier 3 in France, the baseline self-assessment survey includes an additional social and sexual behaviour questionnaire.

**
*Outcome assessment.*
** During the medical assessment on D14, 28, 60 and 180, the clinical status according to a four-point ordinal scale (see the
*Outcomes* section) is recorded.

For participants who are pregnant at any time during the study, they are followed in the study until their pregnancy outcome is known.

*Note:* As participants can consent to enrol in the study at any point after receipt of a positive PCR result for mpox infection, the eCRF can be completed using existing medical notes and results of samples already taken.

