^d^Samples are only collected where feasible and permitted under local and national regulations on mpox infection prevention and control. Where local capacity limits sample collection, sites should prioritise the collection of D14 and D28 samples—all other samples are optional. Baseline samples are the participant’s diagnostic samples, which may have been collected for routine care before study participation commenced.

^e^An additional sample should be collected at D21 if the participant has a positive PCR on D14.

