Detection and quantification of MPXV using different PCR tools from different body samples (skin lesions, mucosal lesions, blood, urine, genital secretions, oropharynx, saliva, anus) at baseline, D8, D14 and D28. Additional samples are collected and tested at D60 and D180 if participants receive a positive result at D28 or D60, respectively;Capacity of MPXV to infect cells, and replicate, investigated by cell culture and MPXV detection from supernatant at baseline;Genetic diversity of MPXV between the participants and between the different anatomical sites, assessed with MPXV deep sequencing;Detection of syphilis using serological test, and other sexually transmitted infections (STIs) (
*Chlamydia trachomatis*,
*Neisseria gonorrhoeae*,
*Mycoplasma genitalium*) using PCR from urine, anus and oropharynx, at baseline;Quantification of HIV viral load from blood and semen in participants living with HIV at baseline, D8, D14 and D28;Description of social and sexual behaviours in the months prior to inclusion;Quantification of plasma antiviral concentrations;Assessment of the diversity of genetic immune host factors;Quantification and dynamic of the humoral and neutralizing memory B cell responses, as well as the cellular T cell response, over time, at baseline, D14, D28, D60 and D180.

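### The protocol gives conflicting rules for D28 PCR sampling; where the conditional rule was followed and unsampled participants are left out, D28 virologic results describe D14-positive participants only

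*Protocol article*

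**What the plan says.** Data collection methods, Biologic sampling, lists blood, lesion and throat samples at D4, D8, D14, D21 and D28. It puts an asterisk on blood, D4, D8 and D21 and explains that this "denotes procedures only for hospitalised subject; day 21 and 28 sampling only if day 14 sample is still positive". The next paragraph of the same section says that where capacity is limited "sites should prioritise the collection of D14 and 28 samples", with no PCR condition.

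Table 1 sides with that second paragraph. Its D28 lesion, throat and blood cells are bold, which the table note defines as priority. Footnote d repeats that "sites should prioritise the collection of D14 and D28 samples" and calls the other samples optional where capacity is limited. Footnote e reads "An additional sample should be collected at D21 if the participant has a positive PCR on D14" and does not mention D28. The sampling rows carry no inpatient limit; the wording about hospitalised patients sits in the medical assessment row.

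The Outcomes section lists D28 among the Tier 1 virologic timepoints without a D14 condition. Under Statistical method, clearance frequency is reported by day and treatment status, changes in throat and blood DNA are compared by linear regression at each timepoint, and "Logistic regressions will model the presence of mpox virus DNA in lesion swabs at each timepoint".

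For Tier 2, the exploratory outcomes say "Additional samples are collected and tested at D60 and D180 if participants receive a positive result at D28 or D60, respectively", while the biologic-sampling text gives "D60 (in case of oral, genital or anal lesion) and D180 (only if sample is positive at D60".

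**The concern.** One sample cannot be both a priority for everyone and taken only after a positive D14 result. The choice fixes the D28 denominator. Under the conditional rule, everyone negative at D14 has no D28 sample by design, and the variable that decides this is an earlier value of the same outcome, measured after treatment may have started. An analysis of sampled participants then estimates D28 positivity given D14 positivity, not D28 positivity in the cohort. If treatment speeds clearance before D14, its successes leave the D28 comparison. If sites followed different rules, the pooled denominator is a mixture. The Sample size paragraph under Statistical method says that treatment availability and prescribing differ across countries, so that mixture could line up with treatment.

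**Working it through.** The protocol states no figure to reproduce: it sets no sample size target and gives no PCR positivity rates. The check has two parts.

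**1. The rules side by side**

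| Sample | Biologic-sampling text | Its next paragraph, Table 1, footnotes d and e |
|---|---|---|
| D28 | only if D14 positive | priority, no PCR condition |
| D21 | hospitalised only, and D14 positive | extra sample if D14 positive |
| D4, D8 | hospitalised only | scheduled in all tiers, optional where capacity is limited |
| Blood | hospitalised only | scheduled in all tiers, D14 and D28 in bold |

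The conflict needs no outside data. The text also does not say which D14 specimen (lesion, throat or blood) must be positive.

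**2. Size of the selection effect**

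Inputs:
- From the Discussion: 601 PCR-confirmed cases enrolled, 55 of them treated with tecovirimat.
- Assumed: p = P(positive at D14), 0.1 to 0.6; q = P(positive at D28 given positive at D14), 0.1 to 0.5; r = P(positive at D28 given negative at D14), 0 to 0.02.

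Formulas: D28 positivity in all participants = p·q + (1 − p)·r. In the D14-positive set it is q. With r = 0 the ratio is q/(p·q) = 1/p.

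*Single example.* p = 0.2, q = 0.3, r = 0: all participants 0.2 × 0.3 = 6% (clearance 94%); selected set 30% (clearance 70%). With r = 0.02 the figure for all participants is 0.06 + 0.8 × 0.02 = 7.6%.

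*Range, r = 0.* All participants: 0.1 × 0.1 = 1% to 0.6 × 0.5 = 30%. Selected set: 10% to 50%. The overstatement factor runs from 1/0.6 = 1.7 to 1/0.1 = 10. With r = 0.02 the range for all participants is 2.8% to 30.8%. The direction is unchanged, but the factor shrinks: at p = q = 0.1 it is 0.10/0.028 = 3.6 instead of 10.

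*Numbers left.* 601 × p gives about 60 to 361 participants with a D28 sample; 55 × p gives about 6 to 33 treated with tecovirimat.

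*Treatment contrast, r = 0, p = 0.2 treated and 0.4 untreated.*
- q = 0.3 in both groups. All participants: 6% v 12%, OR = (0.06/0.94)/(0.12/0.88) = 0.47. Selected set: 30% v 30%, OR = 1.00.
- q = 0.4 treated, 0.3 untreated. All participants: 8% v 12%, OR = (0.08/0.92)/(0.12/0.88) = 0.64. Selected set: OR = (0.4/0.6)/(0.3/0.7) = 1.56, so the direction reverses.

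*Mixed practice.* If a share s of participants falls under the conditional rule, observed positivity is p·q/(s·p + 1 − s). With p = q = 0.3 and s = 0.5: 0.09/(0.15 + 0.5) = 13.8%, against a true 9.0%.

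**The case against.** A reader might infer that D28 positivity will be overstated as a matter of fact. The documents do not support that. It needs two things: that the conditional rule was followed, and that unsampled participants are dropped. Under Table 1 and its footnotes this selection does not arise.

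Nor do they say that PCR endpoints will be analysed on available samples only. The statement that unrecovered endpoints stay missing follows recovery steps written for the time-to-event outcome and the four-point scale. Clearance is called binary without saying how a D14-negative, unsampled participant is classed, and data handling is left to an SAP that is not shown. That SAP could classify these participants sensibly. It cannot settle which sampling rule was in force, because the conflict is in the protocol.

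It is also tempting to call all D4 and D8 results inpatient results. That presumes the asterisk rule governed, which is the point in dispute. Recruitment was partly retrospective and the eCRF may be filled from samples already taken, so actual sampling may match neither rule.

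The numerical examples use chosen rates and show what can happen, not what is likely. The primary outcome is lesion resolution to a maximum of 14 days and uses no D28 PCR. These limits stand, and they lower the weight of the point. They do not remove the contradiction.

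**Conclusion.** The point holds in conditional form and should be fixed. The sampling rules for D28, D4, D8 and blood conflict on the face of the protocol. Where the conditional rule was followed and unsampled participants are left out, D28 clearance, DNA presence and change from baseline describe D14-positive participants only. D28 positivity is then overstated by about 1/P(positive at D14), a factor of 1.7 to 10 over the assumed range if D14-negatives stay negative and less if some turn positive again. A treatment difference can vanish or change sign, and mixed site practice gives a partly selected set. All sizes rest on assumed rates; the contradiction does not. The endpoints affected are secondary or exploratory in a primarily descriptive study, so the primary analysis is not at risk. The Tier 2 mismatch on the D60 trigger (positive D28 result or presence of lesions) is a side note: it is exploratory, confined to France, and does not bear on D28.

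**What to change.** - Reconcile the biologic-sampling text with its next paragraph, Table 1 and footnotes d and e. State which rule was in force, by site or country if it differed, and which D14 specimen triggers resampling. Enrolment has stopped, so the record of what was done matters more than new wording.
- For D28 clearance and DNA presence, do not analyse sampled participants only. Count D14-negative participants not resampled by rule as negative at D28, and add a sensitivity analysis without this assumption.
- For D28 change from baseline, that classification supplies no Ct value. Either set these participants to the assay detection limit as a sensitivity analysis, or label the result as conditional on D14 positivity.
- Report D4, D8 and blood results with the number sampled by inpatient and outpatient status. Label them inpatient results only where that limit was applied.
- Reconcile the Tier 2 D60 trigger between the exploratory outcomes and the biologic-sampling text.

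Cost: wording in the protocol and SAP and a tabulation of sampling practice, with no new samples. The downside is the stated assumption that D14-negatives stay negative, which the sensitivity analysis is there to test.
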